## Abstract

**Background:**

There is emerging evidence to suggest that Crohn’s disease (CD) may be a disease of the mesentery, rather than of the bowel alone. A more extensive mesenteric resection, removing an increased volume of mesentery and lymph nodes to prevent recurrence of CD, may improve clinical outcomes. This study aims to analyse whether more extensive ‘oncological’ mesenteric resection reduces the recurrence rate of CD.

**Methods:**

This is an international multicentre randomized controlled study, allocating patients to either group 1—mesenteric sparing ileocolic resection (ICR), the current standard procedure for CD, or group 2—extensive mesenteric ICR, up to the level of the ileocolic trunk. To detect a clinically relevant difference of 25 per cent in endoscopic recurrence at 6 months, a total of 138 patients is required (including 10 per cent dropout). Patients aged over 16 with CD undergoing primary ICR are eligible. Primary outcome is 6-month postoperative endoscopic recurrence rate (modified Rutgeerts score of greater than or equal to i2b). Secondary outcomes are postoperative morbidity, clinical recurrence, quality of life, and the need for (re)starting immunosuppressive medication. For long-term results, patients will be followed up for up to 5 years to determine the reoperation rate for recurrence of disease at the anastomotic site.

**Conclusion:**

Analysing these two treatment strategies in a head-to-head comparison will allow an objective evaluation of the clinical relevance of extensive mesenteric resection in CD. If a clinical benefit can be demonstrated, this could result in changes to guidelines which currently recommend close bowel resection.

**Registration number:**

NCT00287612 (http://www.clinicaltrials.gov)

## Introduction

Despite an expanding medical armamentarium, up to 75 per cent of patients with Crohn’s disease (CD) need a surgical resection at some point during the course of their disease^1^. Well known indications are stricturing and penetrating disease. Recently, it has been demonstrated that surgical resection can also be beneficial to patients not responding to immunomodulator therapy. The LIR!C trial and its long-term results demonstrated that, in patients with limited ileocaecal disease, an ileocolic resection (ICR) is a favourable treatment option, resulting in better patient-reported quality of life (QoL) and less medical treatment, when compared with escalation treatment with tumour necrosis factor (TNF)-α blockers^2^^,^^3^.

Unfortunately, surgery for CD is not curative. The 6-month endoscopic recurrence rate is estimated to be up to 60 per cent^4^. Within 5 years postoperatively, clinical recurrence is observed in up to 50 per cent of patients^1^. A significant volume of research has been conducted in an attempt to determine how to prevent postoperative recurrence of CD following an ICR. Some studies focussed on the timing of resuming postoperative medications. Others looked at surgical techniques, including the type of anastomosis^5–8^. Other than the potential decreased recurrence with the Kono-S anastomosis^8^, no surgical techniques seem to alter the postoperative recurrence rate of CD following an ICR.

There is emerging evidence to suggest that CD may be a disease of the mesentery, rather than of the bowel alone^9–13^. However, the mesentery is typically left *in situ* during close bowel resection for CD^14^, unlike oncological resections for colorectal cancer. Recently, the first retrospective study on mesenteric resection, alongside ICR, in CD has been published, reporting surgical recurrence rates of 40 per cent in the ICR group without resection of the mesentery, compared with 3 per cent in the ICR group with resection of the mesentery^15^. However, data are difficult to interpret due to the difference in follow-up between the two groups. Prospective data from an RCT are lacking.

## Methods

### Objectives

The primary aim of this study is to prospectively determine the postoperative endoscopic recurrence rates following mesenteric sparing resection *versus* extensive mesenteric resection, when performing an ICR for CD. Endoscopic recurrence is generally considered as an objective and accurate parameter for disease activity, and it has been demonstrated that endoscopic recurrence almost always precedes clinical symptoms^16^.

Results of this study will enable the authors to provide a consensus on current surgical management.

### Study design

The Mesenteric SParIng *versus* extensive mesentereCtomY in primary ileocolic resection for ileocaecal Crohn’s disease (SPICY) trial is a multicentre RCT where participants will be randomized in a 1 : 1 ratio to either group 1—mesenteric sparing ICR, the current standard procedure for CD, or group 2—more extensive mesenteric ICR, up to the level of the ileocolic trunk. The trial will be conducted in Amsterdam University Medical Centre (AUMC) in Amsterdam, Flevo Hospital in Almere, and Maasziekenhuis Pantein in Beugen, the Netherlands; Humanitas Research Hospital in Milan, Italy; University Hospital Leuven in Leuven, Belgium; the Cleveland Clinic in Cleveland, Ohio, USA; and other centres interested in participating in the trial. The multinational participation in this study will greatly facilitate international implementation of the study results. Hospitals will be allowed to start patient accrual after local approval has been obtained.

### Primary and secondary outcomes

The primary outcome is the endoscopic recurrence rate at 6 months following ICR, defined as modified Rutgeerts score of greater than or equal to i2b, as determined by central reading.

Secondary outcomes are postoperative morbidity, clinical recurrence, QoL, and the need for (re)starting immunosuppressive medication postoperatively. For long-term results, patients will be followed up for up to 5 years to determine the reoperation rate for recurrence of disease at the anastomotic site.

### Study population

All eligible patients with CD undergoing primary ICR for terminal ileitis of ileocolic disease will be considered for inclusion. For eligibility to participate in this study, a subject must meet all of the following criteria: adults of either sex, aged 16 years or older; ileo(colic) disease with an indication for primary ileocaecal resection or ICR; subject on any concurrent therapies; terminal ileitis (L1 or L3 disease), previously confirmed by endoscopy, with a recent update (within the last 3 months) of imaging (for example, ultrasound, MRI, CT enterography) before confirmation of eligibility, preferably discussed by the multidisciplinary team; ability to comply with the study protocol; and competency and ability to provide written informed consent.

Concurrent perianal and/or further proximal disease are not exclusion criteria.

A potential subject who meets any of the following criteria will be excluded from participation in this study: inability to give informed consent; patients under the age of 16 years; patients undergoing repeat ICR; clinically significant medical conditions within 6 months before the operation (for example, myocardial infarction, active angina, congestive heart failure, or other conditions that would, in the opinion of the investigators, compromise the patient’s safety); history of cancer of less than 5 years which might influence the patient’s prognosis; emergent operation; pregnancy or breastfeeding; inability to comply with postoperative assessments, imaging and endoscopy; and Kono-S anastomosis.

### Ethical consideration

The trial will be conducted according to Good Clinical Practice guidelines and the principles of the Declaration of Helsinki (2013)^17^. This study is approved by the Medical Ethical Committee of the AMC. The protocol is registered by the Dutch Central Committee on Research Involving Human Subjects (NL61632.018.18).

### Informed consent procedure

Eligible patients with terminal ileitis referred for outpatient counselling for surgical resection will be screened for inclusion criteria at outpatient clinic visits. Patients meeting the inclusion criteria will be offered the opportunity to participate in the trial following multidisciplinary team discussion and will need to sign a written consent form if they would like to be enrolled.

### Randomization

Randomization of consented study participants to either mesenteric sparing ICR or extensive mesenteric ICR will be done using an online-based system for allocation concealment (Castor EDC). Allocation concealment will be ensured, as the service will not release the randomization code until the patient has signed for informed consent and has been recruited into the trial. Randomization will not be stratified. There is no blinding to treatment allocation for the treating surgeon. The treatment will be blinded for all other physicians (for example, gastroenterologists, central readers) and patients. A statistician blinded to treatment allocation will analyse the data.

### Study outline

#### Preoperative

Before surgery, all patients must have had an endoscopy to confirm terminal ileitis, and a recent update (within the last 3 months) of imaging before inclusion (for example, ultrasound, MRI, or CT enterography). The Crohn’s Disease Activity Index (CDAI) score will be determined, and the following Quality of Life (QoL) questionnaires administered: EuroQol-5 Dimension (EQ-5D) questionnaire, 36-Item Short Form Health Survey (SF-36), and Inflammatory Bowel Disease Questionnaire (IBDQ). Baseline characteristics will be collected.

#### Surgery

All surgical procedures will be performed as a laparoscopic resection, with conversion to an open operation only if clinically indicated. For mesenteric sparing resection, the mesentery is divided close to the bowel. In the more extensive mesenteric resection, the mesentery is resected up to the origin of the ileocolic trunk. After identification of the ileocolic pedicle, the lower border of the ileal branch of the ileocolic artery is followed distally until branching into caecal arteries. The rest of the operation will be identical. Care would be taken to ensure the amount of colon resected in both groups is similar (*Figs 1* and *2*). A wide-stapled anastomosis will be performed in all patients, as recommended by current European Crohn’s and Colitis Organisation (ECCO) guidelines. Technical aspects (for example, intra- or extracorporeal anastomosis) will be left at the discretion of the surgeon. The Kono-S anastomosis, and its role in the reduction of postoperative recurrence, is still a subject of research. Therefore, this technique will not be used in the current trial, as it can be considered a confounding variable. Operative data will be collected. Perioperatively, patients will be treated according to the local enhanced recovery pathway.

**Fig. 1 zrab136-F1:**
[figure not shown]
Surgical technique: a More extensive mesenteric resection following the lower border of the ileocolic trunk; b Mesenteric sparing ileocolic resection, conforming to current guidelines.

**Fig. 2 zrab136-F2:**
[figure not shown]
Measurement of length of resected specimen on colonic side 1, caecum and ascending colon; 2, ascending colon.

#### Quality control of surgical procedure

To ensure that the surgical technique in the experimental arm is performed properly in all centres, a quality control assessment will be conducted as follows. A video vignette of the surgical procedure which has been published will be shared with all participating centres as an example^18^. The participating centres will be asked to provide a photo of the resected specimen from all included patients. Each centre will provide one or two videos of the surgical procedure when requested.

#### Postoperative

##### Assessment of endoscopic recurrence

At week 26 (6 months), an ileocolonoscopy with biopsy will be performed, and the modified Rutgeerts score determined, according to current standard guidelines^19^. The procedure will be video recorded for blinded central reading. If a video recording of the endoscopy is not available, photos taken during endoscopy will be evaluated by the same blinded central reading team. A minimum of five photos of the terminal ileum and five photos of the anastomosis are required.

##### Postoperative morbidity

Data on postoperative morbidity will be collected. Adverse events (AE) and severe adverse events (SAE) will be recorded during hospital stay and outpatient visits.

##### Assessment of clinical recurrence

The CDAI score will be determined at 6 and 12 months postoperatively, based on 7-day scoring by the patient.

##### Assessment of quality of life

QoL will be assessed up to 1 year postoperatively. QoL questionnaires will be administered at each visit: EuroQol-5 Dimension (EQ-5D) questionnaire, SF-36, and IBDQ. Patients will complete the questionnaires at baseline, 6 months, and 12 months postoperatively.

##### Medical management

In both arms, patients will be advised to stop all medications postoperatively. If a patient is at high risk of developing clinical recurrence within 6 months after surgery (that is, more than two risk factors according to ECCO guidelines), the patient may receive prophylactic medical treatment postoperatively, at the discretion of the local multidisciplinary team. If clinical recurrence occurs within 6 months, this will have to be confirmed by endoscopy, after which medical treatment can be initiated. Medications can be initiated based on the severity of the endoscopic recurrence and according to the treating physician’s preference.

During follow-up, data will be collected on the medical management of CD to determine the timing of resuming immunosuppressive medications (for example, corticosteroids, immunomodulators, and biologics).

##### Assessment of surgical recurrence

Patients will be followed up for up to 5 years after surgery to determine the reoperation rate for recurrence of disease at the anastomotic site.

### Sample size calculation

The primary endpoint is postoperative endoscopic recurrence of CD at 6 months. This study is powered to detect a difference of 25 per cent in endoscopic recurrence at 6 months between the two randomized surgical techniques, 60 per cent *versus* 35 per cent (a risk reduction of 45 per cent). Assuming a test of two independent proportions powered at 80 per cent, an α-level of 0.05, a total of 62 patients in each surgical arm will be required, for a total enrolment of 124 patients. Allowing for a 10 per cent dropout, the aim is therefore to enrol 138 patients.

### Statistical analysis

All data will be collected into an electronic database, which is the electronic data management system Castor EDC Version 1.4 (https://www.castoredc.com). Outcome parameters will be analysed with appropriate statistical tests by a statistician blinded to treatment allocation on an intention-to-treat basis using the statistical program SPSS^®^ (IBM, Armonk, New York, USA). Descriptive statistics will be used to report baseline patient and surgical variables. The primary outcome of endoscopic recurrence at 6 months following ICR, and secondary outcomes, including postoperative morbidity, clinical recurrence, and need for immunosuppressive medication, in the two surgical arms will be analysed using the chi-square or Fisher’s exact test. Differences in QoL will be analysed using mixed-model analysis of variance for repeated measures. Univariate associations with the risk of recurrence will be assessed using the Cox proportional hazards model, with results reported as hazard ratios (HRs) and 95 per cent confidence intervals. The α-level will be set at 0.050 for statistical significance.

Multiple variable models will be considered in the same way, depending on the number of recurrences identified. The most recent version of the statistical program IBM SPSS Statistics for Windows will be used.

The statistical analysis plan will be finalized before data are locked for analysis, and a decision will be made on planned subgroup analysis and how to deal with protocol violations and potential baseline imbalance.

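### The QoL model should state how the baseline score enters: the natural reading, a three-visit group-by-time ANOVA, uses it less efficiently than baseline adjustment

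*Protocol article*

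**What the plan says.** The Statistical analysis section of the protocol article gives QoL one sentence: "Differences in QoL will be analysed using mixed-model analysis of variance for repeated measures". It does not say which visits form the outcome, whether any covariate is included, or which term or contrast is the treatment comparison.

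The section on assessment of quality of life supplies the schedule: "Patients will complete the questionnaires at baseline, 6 months, and 12 months postoperatively". It names three instruments: "QoL questionnaires will be administered at each visit: EuroQol-5 Dimension (EQ-5D) questionnaire, SF-36, and IBDQ".

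QoL is one of the listed secondary outcomes: "Secondary outcomes are postoperative morbidity, clinical recurrence, QoL, and the need for (re)starting immunosuppressive medication postoperatively". The sample size rests on endoscopic recurrence alone: "This study is powered to detect a difference of 25 per cent in endoscopic recurrence at 6 months between the two randomized surgical techniques". Further detail is deferred: "The statistical analysis plan will be finalized before data are locked for analysis". The same sentence leaves the handling of potential baseline imbalance to that later decision.

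**The concern.** A repeated-measures analysis of variance, applied to a score measured on three occasions with no covariate named, would ordinarily be set up as arm by time with all three occasions as levels of time. That model offers two standard tests, and neither suits a randomised comparison well.

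- **Group main effect.** This averages the arm difference over all three visits. One of them is preoperative, where randomisation means that no true difference exists. An effect of size d at both follow-ups therefore enters as 2d/3.
- **Group-by-time interaction.** With three visits this is a 2-df test of whether change over time differs between arms. It rests on differences from baseline, which carry the full noise of the baseline score, whereas adjustment removes only the part that baseline predicts.

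The trial was sized for a binary primary endpoint, so QoL has whatever power 124 evaluable patients happen to give. A real QoL difference could be missed merely because of how the baseline score, which is collected anyway, enters the model.

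**Working it through.** **Inputs from the protocol article.** Allocation: "participants will be randomized in a 1 : 1 ratio". Sample size: 62 per arm, 124 in total, 138 with 10% dropout, for 60% versus 35%. Test settings: "Assuming a test of two independent proportions powered at 80 per cent, an α-level of 0.05", taken as two-sided because sidedness is not stated.

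**The plan's own figure.** With pooled variance and no continuity correction:

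n = [1.960·√(2·0.475·0.525) + 0.842·√(0.60·0.40 + 0.35·0.65)]² / 0.25² = (1.384 + 0.575)² / 0.0625 ≈ 61.4, so 62 per arm.

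Power at 62 per arm is 80.4%, and 124/0.9 = 137.8, so 138. The stated size reproduces. No stated figure depends on the QoL model.

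**Assumptions for the QoL illustration.** The document gives no QoL SD, effect or correlation. I assume unit SD at each visit, equal correlation r between any two visits (compound symmetry), no missing data, 62 per arm, and an effect d = 0.4 SD at both 6 and 12 months.

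**Variance per patient of each contrast, v** (the variance of the arm difference is 2v/62):

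- Mean of three visits: v = (1 + 2r)/3, with effect 2d/3 = 0.267.
- Mean of follow-ups minus baseline (1 df): v = (1 + r)/2 + 1 − 2r, with effect d = 0.4.
- Mean of follow-ups adjusted for baseline: v = (1 + r)/2 − r², with effect d = 0.4.

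Power for each is Φ(effect/√(2v/62) − 1.96). For the 2-df interaction, the noncentrality is d²/(2v/62) with the change-contrast v, because under a constant effect all the signal lies in that one contrast. Power is the tail of a noncentral chi-square with 2 df beyond its 5% critical value.

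**Worked at r = 0.5.**

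- Main effect: v = 0.667, SE = √(2·0.667/62) = 0.147, ratio 0.267/0.147 = 1.82, power 44%.
- Change: v = 0.75, SE = 0.156, ratio 2.57, power 73%.
- 2-df interaction: noncentrality 0.16/(2·0.75/62) = 6.61, power 63%.
- Baseline-adjusted: v = 0.50, SE = 0.127, ratio 3.15, power 88%.

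**All results, d = 0.4 SD.**

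| Contrast | r = 0.3 | r = 0.5 | r = 0.7 |
|---|---|---|---|
| Group main effect over three visits | 53% | 44% | 38% |
| Group-by-time, 2 df | 48% | 63% | 85% |
| Change from baseline, 1 df | 58% | 73% | 91% |
| Baseline-adjusted | 85% | 88% | 96% |

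At d = 0.5 SD the adjusted analysis again comes first: main effect 72, 62 and 55%; 2-df test 68, 83 and 97%; change 78, 90 and 99%; adjusted 96, 98 and 99.6%.

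**Why adjustment beats change at any r below 1.** The difference between the two variances is (1 − 2r) + r² = (1 − r)², which is positive unless r = 1.

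**Baseline kept in the outcome vector with a common mean.** A three-visit model that constrains the arms to one baseline mean, solved by generalised least squares, gives v = 0.56, 0.50 and 0.36 at r = 0.3, 0.5 and 0.7. These equal (1 + r)/2 − r² at each r. What costs power is therefore the unconstrained baseline together with the contrast tested. Modelling baseline as an outcome does not cost power in itself.

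**The case against.** The strongest objection is that the protocol never says baseline is one of the repeated outcomes. The method sentence names no outcome vector, covariate or contrast, and the schedule says when forms are completed, not how they enter a model. Two follow-up visits are already repeated measures, so the sentence also fits a model of the 6- and 12-month scores adjusted for baseline. Details of a secondary-outcome model commonly belong in the statistical analysis plan, which is not shown. This stands as far as it goes: the three-visit reading is an inference, and an unstated detail alone would be no finding. What keeps the point alive is that the protocol does name a method, lists three occasions and names no covariate. A plan that carries the sentence forward as it stands would most naturally become the unconstrained three-visit analysis.

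A reader might infer three stronger things, none of which the document supports.

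- **That the plan definitely discards baseline information.** The text does not settle this.
- **That placing baseline in the outcome vector is itself a mistake.** It is not: with a common baseline mean it matches adjustment exactly.
- **That QoL power in this trial will be 44% instead of 88%.** That pair belongs to one contrast, which the protocol never says it will test, and to an assumed effect and correlation. The loss against the interaction is smaller at high correlation: 85% versus 96% at r = 0.7.

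The deferral of baseline imbalance does not answer the point. Adjustment is justified by precision whether or not imbalance appears, so it should be fixed beforehand and not made to depend on what the baseline table shows.

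**Conclusion.** The point holds as an improvement to the wording of a secondary analysis, not as an error that invalidates anything. On the natural reading of the protocol, both standard tests of the QoL model are less powerful than a baseline-adjusted comparison using the same data. With a 0.4 SD effect sustained at both follow-ups, the shortfall from adjustment is about 32 to 58 percentage points for the main effect (85 − 53 and 96 − 38) and about 11 to 37 points for the 2-df interaction (96 − 85 and 85 − 48), over correlations of 0.3 to 0.7.

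These sizes rest on assumed effect, correlation and compound symmetry, with no missing data. The advantage over the change contrast holds for any correlation below 1; the ranking against the 2-df test was checked only for an effect that is equal at both visits. The three-visit analysis would still be valid in its type I error. QoL carries no power claim, and the primary analysis and the sample size are untouched.

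**What to change.** Replace the QoL sentence, or specify in the statistical analysis plan before data lock: a linear mixed model for each QoL score with the 6- and 12-month values as outcomes; arm, visit and arm-by-visit as fixed effects; the baseline score as covariate; and within-patient correlation modelled. Report the arm difference with its 95% CI at each visit.

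An equivalent choice is a three-visit model constrained to a common baseline mean in both arms, with the same visit-specific differences reported. It has the practical advantage that patients with a missing baseline form stay in the analysis without a separate rule.

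The cost is wording only. No patients, visits or questionnaires are added, and if the covariate form is chosen, a short rule for missing baseline forms is needed.
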